## Abstract

**Background:**

Chronic obstructive pulmonary disease (COPD) is a common respiratory condition characterised by dyspnoea during daily life. As the disease progresses, people with COPD can experience poor quality of life, reduced exercise capacity, worsening of symptoms and increased hospital admissions. Pulmonary rehabilitation, which includes exercise training, optimises both psychological and physical function, reduces symptoms and mitigates healthcare utilisation in people with COPD. There is, however, a gap in implementation of pulmonary rehabilitation programs, with global access limited to a small fraction of people with COPD. The overall aim of this study is to gather evidence that will optimise the implementation of pulmonary rehabilitation in people with COPD living in Perth, Western Australia.

**Methods:**

This is a mixed methods study protocol informed by a critical realist perspective. The study will comprise four phases. In Phase 1, we will quantify target behaviours of healthcare professionals and people with COPD which are related to the implementation of pulmonary rehabilitation at three tertiary hospitals. In Phase 2, we will conduct semi-structured interviews to explore the determinants of these target behaviours from the perspectives of healthcare professionals, people with COPD and their primary support person. In Phase 3, knowledge gained in Phases 1 and 2 will be used by healthcare professionals and people with COPD to co-create, field test and apply strategies that optimise these target behaviours. In Phase 4, we will re-quantify these target behaviours to determine the influence of co-created strategies. The cost effectiveness of implementing the co-created strategies will be explored by an economic analysis.

**Discussion:**

Understanding current clinical practice and the determinants of target behaviours pertaining to the implementation of pulmonary rehabilitation is crucial when developing strategies that successfully bridge the pulmonary rehabilitation implementation gap. If co-created strategies are effective, more people with COPD living in Perth, Western Australia will have access to pulmonary rehabilitation enabling them to derive the health benefits associated with this intervention.

## Background

Chronic obstructive pulmonary disease (COPD) is a common progressive lung condition characterised by dyspnoea during daily life [1]. In 2017, COPD was the most prevalent chronic respiratory disease globally, with an overall prevalence of 9.8% [2]. Across Australia, approximately 1 in 13 people over the age of 40 have COPD of at least moderate severity [3, 4]. In 2015, COPD was the third highest cause of total disease burden in Australia, costing the healthcare system AU$976.9 million from exacerbations, hospitalisations and medications [5, 6]. As the disease progresses, people with COPD commonly report a deterioration in health-related quality of life, exercise capacity and increased symptoms such as dyspnoea and fatigue during daily life [1, 7]. They are also at an increased risk of experiencing an exacerbation requiring hospitalisation [1, 7]. Pulmonary rehabilitation (PR), which includes exercise training, is an important component in the management of people with COPD [8]. It is well established that in people with stable COPD, PR leads to clinically meaningful improvements in health-related quality of life and exercise capacity, and reduces symptoms such as dyspnoea and fatigue during daily life [9, 10]. There is evidence of a similar effect on these outcomes when exercise training is initiated during or immediately following an exacerbation of the disease [11]. With regard to the healthcare system, PR can reduce healthcare utilisation in both people with stable COPD, and following an exacerbation [11, 12].

Clinical guidelines for the management of people with COPD recommend that PR should be provided to people with stable COPD who experience symptoms during daily life, as well as during or soon after an exacerbation of the disease [7, 8]. Despite guideline recommendations and robust evidence to support its effectiveness [9], PR is underused [13]. In 2015, an international study which included data from Australia, Canada, Ireland, New Zealand, Sweden, the United Kingdom and the United States demonstrated that the proportion of people living with COPD who have access to PR is < 1.2% [14]. Underuse of PR is recognised as an international problem prompting the European Respiratory Society (ERS) and American Thoracic Society (ATS) to call for action to bridge the gap between the documented benefits of PR and implementation issues [13]. In Australia, observational data has shown that nearly half of all people with stable COPD and nearly three-quarters of those following an exacerbation of the disease who may benefit from PR are not referred to PR [15, 16]. Healthcare professionals (e.g. Physicians, General Practitioner’s, Physiotherapists) report barriers to PR referral such as limited knowledge of its benefits, uncertainty around program details (i.e. referral processes, location, content and duration of the program), and limited time to discuss and refer to PR [17–19]. The failure to discuss and advocate for PR in the in-patient and out-patient setting leaves people with COPD largely unaware of both the existence of PR programs and its health benefits. Of equal concern are data showing that of those referred to PR, approximately one third do not attend their initial assessment or commence the program [20, 21]. Reasons provided by people with COPD for not attending an initial assessment for PR or choosing not to commence supervised exercise classes relate their perception of limited benefit of such programs and the claim that they are ‘already completing their own exercise’. [19, 22–24] Following an exacerbation of the disease, feelings of low self-worth and being ‘too unwell’ to exercise also reduce the willingness to accept a referral, attend an initial assessment, commence and adhere to an exercise program [25, 26]. Once people with COPD commence PR, the challenge becomes adherence to the program; however, non-completion rates vary internationally. Observational data from Australia, for example, have shown that people with stable COPD who commence PR attend most sessions [16], suggesting that engagement in PR (through referral and attendance to an initial assessment) is the most crucial hurdle to overcome. Earlier work mapping the PR pathway in people with COPD has used retrospective audits of medical records or simple questionnaires over a short period of time [16, 20, 27, 28]. These studies offer an incomplete picture of the PR pathway and barriers to PR. There is a need to prospectively map the full PR pathway in people with COPD, and acquire a comprehensive understanding of the complexities of behaviours which drive the implementation of PR programs, from the perspectives of both healthcare professionals and people with COPD.

The overall aim of this mixed methods study is to gather evidence that will optimise the implementation of PR in people with COPD living in Perth, Western Australia (WA). The research questions to be answered are as follows:
In people with COPD, what is current practice, quantified as specific target behaviours pertaining to the implementation of PR at three tertiary hospitals?From the perspectives of healthcare professionals, people with COPD and their primary support person, what are the barriers and facilitators to the target behaviours pertaining to the implementation of PR?What strategies can be co-created by healthcare professionals and people with COPD with the goal of optimising target behaviours pertaining to the implementation of PR in people with COPD?What is the influence of co-created strategies (from research question 3) on the target behaviours pertaining to the implementation of PR at three tertiary hospitals?

## Methods/design

### Overview

This project will be a 2-year mixed method, co-creation research study undertaken across Fiona Stanley Hospital (FSH), Royal Perth Hospital (RPH) and Sir Charles Gairdner Hospital (SCGH) in Perth, WA. The project has been approved by the Human Research Ethics Committee for the South Metropolitan Health Service (RGS0000003704) with reciprocal approval obtained from the Human Research Ethics Committees for Royal Perth Hospital, Sir Charles Gairdner Hospital, and Curtin University (HRE2020–0095). The research questions will be answered across four consecutive five-month phases (see Fig. 1).

**Fig. 1 Fig1:**
[figure not shown]
Study design flow diagram

Data collection for this project commenced in August 2020, and will continue until April 2022. A steering committee has been established which comprises the research group and clinicians from all three sites. The committee meets monthly via teleconference to discuss conduct of this study and ensures fidelity during data collection.

### Philosophical positioning

Knowledge of our philosophical perspective is essential for appreciating our construction of knowledge (methodology). The design of this project is informed by a critical realist perspective in which ontology (the nature of reality) and epistemology (the nature of knowledge) are considered as two distinct, separate entities. A key feature of a critical realist perspective is that reality exists independently of human awareness [29]. Observation can increase one’s confidence in the existence of reality, but observation does not dictate it. Reality from a critical realist perspective sees the world divided into the real (co-occurrence of causal mechanisms that may influence events and experiences), actual (events and experiences caused by causal mechanisms) and empirical (observable events or actual experiences) domains [30]. Critical realism seeks to develop *empirically supported explanations* of phenomena via questions of how, why, and under what conditions [31]. It encourages researchers to delve beyond empirical observations to understand what causes particular events and behaviours; acknowledging that some claims may be better approximations of reality than others, and recognising that knowledge of these realities is socially produced, temporally transient, and fallible in nature because of the separation of ontology and epistemology [32]. Critical realism rejects social constructivism notions that knowledge is constructed through interaction with others; rather, it acknowledges that we have individual experiences and there are different perspectives on reality [33]. The separation of ontology and epistemology seen within critical realism allows for methodological plurality. Consistent with the notion of ‘fit for purpose’ [29], our methodological approach involves both quantitative and interdisciplinary qualitative methods to generate insight on the interrelationships between context, mechanisms, and outcomes across four phases. Phases 1 and 2 will enable us to construct knowledge through the three layers of reality. Phase 1 contributes to the *actual* layer of reality via quantification of current clinical practice of target behaviours (see Table 1) pertaining to the implementation of PR in Perth. Phase 1 also contributes to the *real* layer of reality via the identification of factors such as gender, current smoking status, and social support which activate causal mechanisms and therefore may influence the *actual* reality observed across Phase 1. Phase 2 contributes to the *empirical* layer of reality where we will explore experiences of healthcare professionals and people with COPD to understand their capability, opportunity, and motivation to fulfil target behaviours (outlined in Table 1). In Phase 3, knowledge constructed through these three layers of reality will be used as a basis to co-create strategies that optimise how PR is implemented. Phase 4 will see clinical practice of PR implementation re-quantified, with potential to demonstrate change in the *actual* layer of reality with co-created strategies in place.

**Table 1 Tab1:** Target behaviours to be quantified in Phase 1 and 4

	Adults hospitalised with an exacerbation of COPD	Adults with COPD who attend Respiratory Medicine out-patients
**Referral to PR**	Proportion referred to PR prior to or within 2 weeks of hospital discharge.	Proportion referred to PR within 2 weeks of attendance at a Respiratory Medicine clinic appointment.
**Attendance to an initial appointment**	Proportion who attend an initial assessment with a Physiotherapist to determine suitability to enrol into an exercise training program.	Proportion who attend an initial assessment with a Physiotherapist to determine suitability to enrol into an exercise training program.
**Commence PR**	Proportion who attend at least one exercise training session overseen by a Physiotherapist.	Proportion who attend at least one exercise training session overseen by a Physiotherapist.
**Attendance to PR**	Proportion who attend ≥80% of the scheduled exercise training sessions overseen by a Physiotherapist.	Proportion who attend ≥80% of the scheduled exercise training sessions overseen by a Physiotherapist.
**Provision of a maintenance strategy**	Proportion who are referred to a maintenance program on completion of exercise training sessions overseen by a Physiotherapist.	Proportion who are referred to a maintenance program on completion of exercise training sessions overseen by a Physiotherapist.

*Abbreviations*: *COPD* chronic obstructive pulmonary disease, *PR* pulmonary rehabilitation

### Phase 1: observing target behaviours of healthcare professionals and people with COPD to quantify current implementation of PR

The aim of Phase 1 is to record target behaviours of healthcare professionals and people with COPD to quantify current implementation of PR in people with COPD. This phase will recruit people with COPD who are currently hospitalised with an exacerbation of their condition (i.e. in-patients) as well as people with COPD who are attending Respiratory Medicine out-patient clinics (i.e. out-patients) at any of the three tertiary hospitals. The target behaviours to be quantified are: referral to PR, attendance at an initial assessment, commencement of supervised exercise training classes, adherence to supervised exercise training and provision of a maintenance strategy on program completion (see Table 1).

#### Inclusion criteria

The inclusion criterion for in-patients will be people admitted to one of the three tertiary hospitals with a primary diagnosis of an exacerbation of their COPD. Exclusion criteria are as follows: (i) admitted to the intensive care unit at time of recruitment (ii) unable to ambulate independently and safely, (iii) have cognitive impairment or an inability to understand English, (iv) living in supported residential care prior to admission and/or (v) not expected to survive the admission (i.e. deemed terminal). Cases will be found by undertaking a daily screen of admissions to specific wards across the three tertiary hospitals using the hospital electronic data system.

The inclusion criterion for out-patients will be people who meet the spirometric criteria for COPD (i.e. post bronchodilator forced expiratory volume in 1 s / forced vital capacity [FEV_1_/FVC] < 0.7) [1]. Exclusion criteria include: (i) completed PR within the previous 12 month period, (ii) attend maintenance PR classes within the previous 8 week period, (ii) unable to ambulate independently and safely, (iii) have cognitive impairment or an inability to understand English, (iv) living in supported residential care and/or (v) have an expected survival of less than 6 months. Cases will be found by daily screening Respiratory Medicine clinic lists at the three tertiary hospitals.

#### Informed consent and data collection

Each person who meets the study criteria will be approached and invited to provide written informed consent to participate in Phase 1. Thereafter, the journey of each participant will be tracked with their data collected using Research Electronic Data Capture (REDCap) data collection tools [34] regarding: (i) referral to PR, (ii) attendance to initial assessment (or reason for non-attendance), (iii) commencement of supervised exercise training (or reason for non-commencement), (iv) adherence to PR (or reasons for non-adherence) and (v) provision of a maintenance strategy on PR completion (see Table 1). Researchers and research assistants will prospectively extract these data; (i) using the participant’s medical records, (ii) via discussion with the participant (either in person or via telephone call) and, (iii) via discussion with the treating Physiotherapist. Research assistants involved in data collection have been provided with standardised training and resources, and meet weekly via teleconference ensure fidelity during data collection. The REDCap data collection tools and resources for research assistants can be found on our Open Science Framework website [35].

### Phase 2: exploring the determinants of target behaviours from the perspectives of healthcare professionals, people with COPD and their primary support person

The aim of Phase 2 is to explore the determinants of behaviours related to referral to PR, initial appointment attendance, commencement of PR, adherence to PR and provision of a maintenance strategy on PR completion. Semi-structured interviews will be conducted to gain perspectives of healthcare professionals (across all three sites), people with COPD and where possible their nominated primary support person.

#### Informed consent

During the process of obtaining informed consent for Phase 1, participant’s interest in engaging in Phase 2 and/or Phase 3 of the project will be ascertained. Expression of interest to participate in Phase 2 will be sought via email from healthcare professionals (e.g. Physicians, Nursing, Physiotherapy and other Allied Health Professionals) who are involved in the management of people with COPD. Healthcare professionals, people with COPD and, where possible, their primary support person will be recruited using purposeful sampling and approached for written informed consent to participate in Phase 2. Purposeful sampling ensures a diverse representation of people with COPD (e.g. smokers vs. non-smokers, have vs. have not attended PR, few vs. multiple co-morbid conditions, have vs. have not had been hospitalised for an exacerbation of COPD within the previous 12 months) and healthcare professionals (e.g. Medical, Nursing, Allied health).

#### Interview structure

A behavioural analysis will be conducted to understand the barriers and facilitators to fulfilling the target behaviours pertaining to PR implementation from the perspectives of healthcare professionals, people with COPD and their primary support person. All interviewees will be asked to comment on their capability, opportunity, and motivation [36] to achieve the target behaviours related to PR implementation. Interview questions to explore specific barriers and enablers will be iteratively developed from Phase 1, and will be based on the Theoretical Domains Framework [37], which is a comprehensive framework for the identification and description of factors that influence behaviour. Data-prompting techniques, such as sharing the results of Phase 1 and photos of adults hospitalised with an exacerbation of COPD (from the internet), will be used to probe barriers and facilitators of PR target behaviours. Interviews will be recorded and transcribed verbatim.

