### Phase 4: evaluating the influence of co-created strategies on target behaviours pertaining to PR implementation

The aim of Phase 4 is to evaluate the influence of co-created strategies on target behaviours pertaining to PR implementation at the three tertiary hospitals. With the co-created strategies in place, using the methodology described for Phase 1, target behaviours of referral to PR, attendance to initial appointment, commencement of PR, adherence to PR and provision of a maintenance strategy on PR completion will be re-quantified at each site. At the end of Phase 4, workshop participants (i.e. the co-creators) will re-convene. During this workshop, the influence of co-created strategies on target behaviours will be shared and feedback will be sought to ensure the strategies are representative of co-creators opinions and intended purpose [38, 39].

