### Sample size

#### Phase 1 and 4

Using data from the 2018 calendar year from one of the included sites (RPH), there were 1357 cases discharged with a diagnosis of an exacerbation of COPD. Assuming similar numbers across all three sites, over a 5 month period, more than 1000 people will be admitted for an exacerbation of COPD. There are likely to be a similar number of people seen in Respiratory Medicine clinics for COPD over the same time period. Therefore, even following application of exclusion criteria, we anticipate access to a large sample (approximately 2000 participants, across all three sites for both Phase 1 and Phase 4) for analysis.

#### Phase 2 and 3

Regarding Phase 2, a sample will be recruited to reach balance between a sample that is too large (which presents feasibility issues for a detailed analysis) and too small (which is unlikely to achieve rich, contextual appreciation of the interview questions). It is estimated that 15 healthcare professionals and 15 people with COPD (with or without their primary support person) will be recruited to Phase 2. Similarly, regarding Phase 3, an adequate sample size will be recruited to encourage collaboration between healthcare professionals and people with COPD, without being too large which may hinder participation of the co-creators. It is estimated that 10 to 12 participants will be recruited to Phase 3 as co-creators.

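### Phase 1 results are shown to treating clinicians in Phase 2, and the Phase 1 versus Phase 4 comparison cannot separate any effect of this from the co-created strategies

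*Protocol article*

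**What the plan says.** The Phase 2 sections of the protocol article plan semi-structured interviews with professionals from all three hospitals. They are invited by email from among those "who are involved in the management of people with COPD", and the disciplines listed include medicine, nursing, physiotherapy and other allied health. Every interviewee is asked about capability, opportunity and motivation to achieve the target behaviours. Under Interview structure, "Data-prompting techniques, such as sharing the results of Phase 1" is given as one example of a prompt. On numbers, the Sample size section says: "It is estimated that 15 healthcare professionals and 15 people with COPD (with or without their primary support person) will be recruited to Phase 2".

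The Overview sets four consecutive phases of five months each. Strategies are created, field tested and applied in Phase 3. Table 1 lists five target behaviours for Phases 1 and 4. The first, for in-patients, is: "Proportion referred to PR prior to or within 2 weeks of hospital discharge".

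The Data analysis section applies segmented regression to data from Phases 1 and 4, with monthly points over five months on each side as the example. The stated aim of Phase 4 is to "evaluate the influence of co-created strategies on target behaviours", and research question 4 is framed in the same way. The Economic analysis section takes the change from the interrupted time series, models its cost implications as those of the strategies, and names the costs to be collected as those of delivering the strategies and the rehabilitation that follows.

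**The concern.** Showing clinicians data on current practice and then discussing their motivation to refer could itself change what they do. The article's Background makes this plausible, since it lists limited knowledge of the benefits and uncertainty about referral processes among the barriers that professionals report. The exposure falls in Phase 2, after the baseline has been measured and before any strategy exists.

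Three statements depend on how the change is attributed: the answer to research question 4, the promise in the Discussion that the interventions will be defined well enough to be reproduced, and the cost model. If part of the change came from the Phase 2 exposure, a hospital adopting only the strategies would omit that part. The economic model would also count its effect while leaving out its cost.

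**Working it through.** **Timeline.** Four consecutive five-month phases give:

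| Phase | Months | Event | Target behaviours measured? |
|---|---|---|---|
| 1 | 1–5 | Baseline | Yes |
| 2 | 6–10 | Interviews, Phase 1 results used as a prompt | No |
| 3 | 11–15 | Strategies created, tested, applied | No |
| 4 | 16–20 | Re-measurement | Yes |

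**Can the two effects be separated?** Write the monthly proportion as

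y(t) = b0 + b1·t + b2·F(t) + b3·S(t) + b4·S(t)·(t − 16),

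where F(t) = 1 from month 6 (data sharing) and S(t) = 1 from month 16 (strategies in place). In months 1–5, F = S = 0. In months 16–20, F = S = 1. The two columns are identical in every observed month: the design matrix has 5 columns and rank 4. Only b2 + b3 can be estimated. Starting S anywhere in months 11–15 changes nothing, because no data are planned there. An analysis plan cannot resolve this with the data described.

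**How large could the exposure effect be?** The documents give neither the number of referring clinicians nor any expected effect of data sharing, so both inputs are assumptions. Let f be the share of referral decisions made by interviewed clinicians and u the absolute rise in their referral rate. The overall shift is f × u, in percentage points:

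| f | u = 5 | u = 10 | u = 20 |
|---|---|---|---|
| 5% | 0.25 | 0.5 | 1 |
| 10% | 0.5 | 1 | 2 |
| 25% | 1.25 | 2.5 | 5 |
| 50% | 2.5 | 5 | 10 |

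**A yardstick.** The article's only figure for patient numbers can be reproduced: 1357 discharges a year at one site × 3 sites × 5/12 = 1696, consistent with its statement of more than 1000 in-patients per five months. Take, for illustration, 1000 patients per phase in one patient group, two-sided alpha 0.05 and 80% power (the article states neither alpha nor power). For baseline referral take 25% and 50%, read from the Background's statement that nearly three-quarters after an exacerbation and nearly half with stable disease are not referred. The simple two-proportion detectable difference is about 5.7 points at 25% and about 6.3 points at 50%. This is not the power of the segmented regression; it only gives scale. Shifts of 0.25–2 points lie well below it. A shift of 5 points approaches it, but needs f = 25% with u = 20, or f = 50% with u = 10.

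**The case against.** The strongest reply is that the exposure is slight. About 15 volunteers across three hospitals is an average of five per hospital, from mixed disciplines, and the article does not say how many of them make referrals. Results are shared as a prompt to probe barriers, which is not an audit-and-feedback programme. Several of the five behaviours, such as attending the first assessment or at least 80% of sessions, depend largely on patients. This stands, and it is why no size can be claimed. It does not make attribution to the strategies alone correct, since the design cannot show that the other component is negligible. Dilution may also be weaker for steps that run through physiotherapists, who are among those invited, although that is inference.

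A reader might go further in four ways that the documents do not support:

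- **That clinicians see their own hospital's results.** The article speaks only of Phase 1 results and does not say whether they are broken down by site.
- **That the steering committee adds to the exposure.** The article says "A steering committee has been established which comprises the research group and clinicians from all three sites", but describes its business as study conduct and fidelity of data collection. It does not say that referral results are shown there.
- **That the framing workshop is further exposure before co-creation.** It opens the Phase 3 workshops and is the first step of co-creation.
- **That the Phase 4 result is biased upward.** This is possible, but neither the direction nor the size is established.

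It can also be said that the co-creation checklist and process evaluation will report how co-creators were upskilled and what evidence they reviewed. That helps reproducibility, but it does not change what the regression can attribute.

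**Conclusion.** The point holds as a limit on attribution. Phase 2 data sharing is a possible co-intervention that precedes the strategies, and with behaviours measured only in Phases 1 and 4 and no concurrent control described, its effect on referral or other clinician-driven behaviours cannot be distinguished from theirs. This follows from the stated timetable and needs no assumption about size.

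The size is unknown. Under the assumed inputs it runs from 0.25–2 points, if interviewees account for 5–10% of referral decisions, to 5 points or more if they account for a quarter to a half with uplifts of 10–20 points (2.5 points at a quarter and 10), or if results spread to colleagues. The documents give no ground for preferring one part of that range. The defect is a mismatch between what research question 4, the Phase 4 aim and the cost model claim and what the design can show. It is worth correcting because the correction is cheap and changes what the trial can properly conclude.

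**What to change.** 1. **Reword the claim.** In research question 4, the Phase 4 aim and the Economic analysis section, describe the result as the change associated with the whole programme: sharing of Phase 1 data, interviews, co-creation and strategies.
2. **Align the costs.** Include the cost of data sharing, interviews and co-creation in the economic analysis, or state that it is excluded.
3. **Optional.** Log which clinicians were shown Phase 1 results and when. Then run a sensitivity analysis excluding patients of clinicians who were interviewed but were not co-creators. Apply the exclusion to both Phase 1 and Phase 4: filtering one phase only would bias the change if volunteers already refer differently from their colleagues. Keep co-creators' patients, because removing them could remove part of the strategy effect. The analysis remains partial, since results may spread to clinicians who were not interviewed.

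The cost is a less specific claim and, for the optional step, a little extra record-keeping and a somewhat smaller sample in that one analysis.
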